technique and one of the important methods to correct tricuspid regurgitation. Mainly suturing the enlarged anterior and posterior annulus, the annulus attached to the free wall of the right ventricle is reduced so that the orifice can accommodate only two to two finger half-widths, thereby correcting tricuspid insufficiency. At present, the mainstream view at home and abroad believes that this plasty method only uses suture annular suture, which is a temporary support method, and the surgical effect is not very clear. West China Hospital has compared 148 patients who underwent tricuspid valvuloplasty and prosthetic annuloplasty in their cardiac surgery department, and De Vega valvuloplasty is not ideal for correcting tricuspid regurgitation. However, some scholars, such as Parolari et al., summarized a meta-analysis published in 2017 that found no significant difference in long-term (up to 15 years) survival rates between the ring-forming and linear-forming methods. In 2016, Shinn from the MayoClinic and his colleagues analyzed 479 patients who underwent tricuspid valve repair concurrently with mitral valve surgery between 1995 and 2010. The primary cause was degenerative diseases, including rheumatic and ischemic conditions. The tricuspid valve repair methods included artificial soft ring implantation (54%), Key repair, or De vega repair (46%). The overall five-year survival rate was 69%, and the ten-year survival rate was 44%; the study also noted that there was no significant difference in late survival rates or the durability of tricuspid valve repair between artificial valves and De Vega repair.

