| 5 Fatal bleeding        | 5a | Possible fatal bleeding; non-pathological or imaging basis but clinically suspicious                                                                                                                                                                                                                                                                                                                                     |
|                         | 5b | Determine the presence of fatal bleeding with obvious signs of bleeding or with pathological or imaging evidence                                                                                                                                                                                                                                                                                                         |

- Severe damage to cardiac or other body structures related to the trial device.
- Infective endocarditis related to the trial device.
- Thromboembolic events related to the trial device: Defined as myocardial

infarction, cerebral infarction, or organ embolism caused by thrombosis, with clinical or imaging evidence of arterial occlusion.

**7.1.7.2.2** Surgical details and intraoperative complications will be recorded in the electronic case report form (eCRF). Safety evaluations will be conducted at discharge/30 days, 3 months, 6 months, 12 months, and annually from 2 to 5 years postoperatively, recording all adverse events. All eCRF data will be submitted to the statistical center for clinical data analysis and evaluation.

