### **7.1.8 Trial Endpoints**

Primary endpoint: The success rate of valve annuloplasty repair at 6 months postoperatively, defined as no severe regurgitation and an increase in diameter  $\leq 15\%$  (based on a comprehensive assessment of regurgitation severity and diameter increase).

Secondary endpoints:

**7.1.8.1** At discharge or 30 days postoperatively (whichever comes first), 3 months, 6 months, and 12 months:

**7.1.8.1.1** Degree of valve regurgitation assessed by echocardiography (evaluated according to the tricuspid regurgitation assessment index table).

**7.1.8.1.2** Changes in echocardiographic parameters (right atrial and ventricular size, diameter, width of the narrowest regurgitation jet, and reverse flow area).

**7.1.8.1.3** NYHA functional class.

**7.1.8.1.4** Freedom from reoperation due to tricuspid valve insufficiency.

**7.1.8.2** Evaluation of the trial device's performance, including needle insertion smoothness and user-friendliness of the ring holder.

**7.1.8.3** Technical success rate of the surgery (before leaving the operating room), defined as no intraoperative death, successful implantation of the annuloplasty ring, successful removal of the ring holder, and no emergency surgery or secondary intervention related to the trial device.

**7.1.8.4** At discharge or 30 days postoperatively (whichever comes first), 3 months, 6 months, and 12 months:

**7.1.8.4.1** Incidence of serious adverse events, including cardiovascular death, major bleeding, severe damage to cardiac or other body structures, infective endocarditis, and thromboembolic events related to the trial device.

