#### **8.1.6 Analysis of Secondary Endpoints**

##### **8.1.6.1 Analysis of Secondary Efficacy Endpoints**

**8.1.6.1.1** Echocardiographic assessment of valve regurgitation severity at discharge or 30 days, 3 months, 6 months, and 12 months post-surgery will be compared between groups using the Cochran-Mantel-Haenszel (CMH) test.

**8.1.6.1.2** Changes in echocardiographic parameters (right atrial size, right ventricular size, radial value, width of the narrowest part of the regurgitant beam, and area of reverse blood flow) at discharge or 30 days, 3 months, 6 months, and 12 months post-surgery will be compared using the t-test.

**8.1.6.1.3** NYHA cardiac function classification at discharge or 30 days, 3 months, 6 months, and 12 months post-surgery will be compared between groups using the CMH chi-square test or rank-sum test.

**8.1.6.1.4** The risk of reoperative tricuspid valve surgery, performance of the test instrument, and success rate of the surgical technique due to tricuspid valve insufficiency will be compared using the chi-square test or Fisher's exact test.

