##### **8.1.6.2 Secondary Safety Endpoint Analysis**

**8.1.6.2.1** The incidence of device-related serious adverse events (SAEs) at discharge or 30 days, 3 months, 6 months, and 12 months post-surgery will be compared between groups using the chi-square test or Fisher's exact test.

**8.1.6.2.2** The incidence of all-cause mortality at discharge or 30 days, 3 months, 6 months, and 12 months post-surgery will be compared using the chi-square test or Fisher's exact test.

**8.1.6.2.3** The incidence of cardiovascular death related to the test device at discharge or 30 days, 3 months, 6 months, and 12 months post-surgery will be compared using the chi-square test or Fisher's exact test.

**8.1.6.2.4** The incidence of major bleeding related to the test device at discharge or 30 days, 3 months, 6 months, and 12 months post-surgery will be compared using the chi-square test or Fisher's exact test.

**8.1.6.2.5** The incidence of severe damage to cardiac or other body structures related to the test device at discharge or 30 days, 3 months, 6 months, and 12 months post-surgery will be compared using the chi-square test or Fisher's exact test.

**8.1.6.2.6** The incidence of device-related infective endocarditis at discharge or 30 days, 3 months, 6 months, and 12 months post-surgery will be compared using the chi-square test or Fisher's exact test.

**8.1.6.2.7** The incidence of thromboembolic events related to the test device at discharge or 30 days, 3 months, 6 months, and 12 months post-surgery will be compared using the chi-square test or Fisher's exact test.

**8.1.6.2.8** The incidence of adverse events from postoperative to 5-year follow-up will be compared using the chi-square test or Fisher's exact test.

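### The 5-year adverse-event comparison in 8.1.6.2.8 is a crude proportion with no allowance for unequal follow-up, so loss to follow-up can bias it in either direction

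*Protocol*

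**What the plan says.** Section 8.1.6.2.8 reads: "The incidence of adverse events from postoperative to 5-year follow-up will be compared using the chi-square test or Fisher's exact test". The safety schedule in 7.1.7.2 runs over the same period: "Safety evaluations will be conducted at discharge/30 days, 3 months, 6 months, 12 months, and annually from 2 to 5 years postoperatively". Under 7.2.7 the visits at years 2 to 5 are telephone contacts that record adverse events.

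The other long-term outcomes stop earlier. Section 8.1.6.2.2 compares "The incidence of all-cause mortality at discharge or 30 days, 3 months, 6 months, and 12 months post-surgery" with the same two tests. Section 8.1.6.1.4 applies them to "The risk of reoperative tricuspid valve surgery, performance of the test instrument, and success rate of the surgical technique" and names no time point there, but 7.1.8 lists "Freedom from reoperation due to tricuspid valve insufficiency" among the endpoints assessed "At discharge or 30 days postoperatively (whichever comes first), 3 months, 6 months, and 12 months".

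Three other sections bear on the denominator:

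- Section 8.7 fills in missing values for the main indicators only and analyses everything else as collected.
- Section 8.9 assigns safety to the safety set (randomized, implanted, with post-implant safety data). It does not say how a patient lost before a time point is counted.
- Section 8.4 gives an expected loss of about 10%, without tying it to 6 months, 12 months or 5 years.

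**The concern.** A chi-square or Fisher test on the proportion with an event treats every patient in the denominator as if observed for the whole period. Over five years of mainly telephone contact that is unlikely to hold. Section 7.1.5.3 declares a patient lost only after three missed visits without contact, and lets investigators withdraw patients for adverse events or disease progression. Section 7.1.3 lists randomization, training and monitoring as the measures against bias, but not masking, so equal loss in the two arms cannot be taken for granted.

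What is at stake is the long-term safety evaluation, which section 3.2 gives as the purpose of years 2 to 5. A difference in follow-up between arms could appear as a difference between devices, or could hide one. This is more than a detail left to the statistical analysis plan, because the protocol itself names the test. An analysis plan that used time-to-event methods for this comparison would depart from it.

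**Working it through.** The protocol states no expected adverse-event rate and no precision for this comparison, so there is no figure of its own to reproduce. The check is an illustration.

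**Inputs.** From the protocol: 82 patients per arm (8.2.1), two-sided 5% tests (8.3), loss of about 10% (8.4). Assumed: a true 5-year risk of 40% in both arms; loss of 10% to 30% over five years, including unequal loss; constant hazards; loss independent of events.

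**Formula.** With true risk p and loss d over the period, set a = −ln(1 − p) and c = −ln(1 − d). The proportion with an event seen before loss is

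crude = a/(a + c) × [1 − (1 − p)(1 − d)].

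**Lost patients kept as event-free.** For p = 0.40, a = 0.5108.

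- d = 0.10: c = 0.1054. Crude = 0.5108/0.6162 × (1 − 0.60 × 0.90) = 0.8290 × 0.46 = 38.1%.
- d = 0.30: c = 0.3567. Crude = 0.5108/0.8675 × (1 − 0.60 × 0.70) = 0.5888 × 0.58 = 34.2%.

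Both are below the true 40%.

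**Event-free lost patients dropped.** The denominator becomes patients with an observed event plus event-free completers, whose share is (1 − p)(1 − d).

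- d = 0.10: 0.3813/(0.3813 + 0.54) = 41.4%.
- d = 0.30: 0.3415/(0.3415 + 0.42) = 44.8%.

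Both are above 40%. The same data give opposite bias under the two denominators.

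**Between-arm comparison, identical devices.** With lost patients kept, loss of 10% against 30% gives 38.1% against 34.2%, a gap of 4.0 points before rounding (38.13 − 34.15). The standard error of the difference with 82 per arm is √(0.3813 × 0.6187/82 + 0.3415 × 0.6585/82) = 7.5 points, so the gap is about half a standard error. Exact binomial enumeration of the uncorrected chi-square test gives a rejection rate of 8.0%, against 4.75% with no loss. With a milder imbalance of 5% against 15%, the gap is 1.9 points and the rejection rate 5.5%.

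**At 12 months.** With 10% loss and lost patients kept, a true 5% shows as 4.75% and a true 10% as 9.5%, so 0.25 to 0.5 point too low. With a true 10% and loss of 5% against 15%, the rejection rate is 5.0%, against 4.9% with no loss.

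**The case against.** The case against giving this much weight is strong, and most of it stands.

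- **Horizon.** A reader might infer that mortality and reoperation are also compared as crude proportions to 5 years. The documents do not support that: both stop at 12 months, where the effect is negligible. Section 4.2 does cite a repair series in which "The overall five-year survival rate was 69"%, and one could calculate a bias in 5-year mortality from it, but no such comparison is planned. That series also had concurrent mitral surgery, and 4.2 cites another repair series with 98.4% five-year survival.
- **Direction.** A reader might infer that the reported rates must be too low. That holds only if lost patients stay in the denominator, which 8.7 and 8.9 do not settle.
- **Death.** A reader might also infer that a patient who dies counts as event-free in 8.1.6.2.8. Section 13.2 makes death a serious adverse event, so such a patient has an event. For non-fatal events with death as a competing event, cumulative incidence without censoring equals the crude proportion. The bias shown here comes from loss, not from death.
- **Inputs.** Both arms have the same telephone schedule. The absence of described masking does not show that loss will differ. Loss above 10%, and any imbalance, are assumptions.
- **Role.** This is a secondary safety comparison. It plays no part in the 6-month non-inferiority test or in the registration application that follows it.

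What survives is narrow: for this one analysis the protocol names a test that ignores follow-up time and leaves the denominator open.

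**Conclusion.** The point holds for the 5-year adverse-event comparison in 8.1.6.2.8, and its severity is minor. The comparison can be biased by loss to follow-up; the protocol does not determine by how much or in which direction. Under the assumptions above (constant hazards, independent loss, true risk 40%), the distortion runs from about 2 points at 10% loss to about 6 points at 30% with lost patients kept, and from about 1 to 5 points the other way with event-free lost patients dropped. A false difference between identical devices becomes somewhat more likely only if loss differs clearly between arms. With near-complete follow-up, or events mostly around surgery, the bias is close to nil. The 12-month comparisons are little affected and the primary decision not at all.

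**What to change.** In 8.1.6.2.8, replace the crude chi-square or Fisher comparison with one of the following, with every patient in the safety set contributing from implantation:

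- cumulative incidence to 5 years, censored at last contact, with death as a competing event for non-fatal events, compared by Gray's test (or the log-rank test where death counts as an event); or
- exposure-adjusted event rates per patient-year.

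Optionally, use Kaplan-Meier estimates for all-cause death and cumulative incidence for reoperation to 12 months, and keep Fisher's test for the discharge/30-day counts. The gain there is small.

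The cost is wording and minor programming, plus one data item: the date of last contact must be captured at each telephone visit, and 7.2.7 and the visit table do not list it. Neither method removes bias when loss is related to the outcome, so the number still under follow-up should be reported by arm and year.

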
It is planned to issue a summary report to the China Food and Drug Administration after the 6-month follow-up of the subjects is completed. A one-year follow-up report will be issued after the 12-month follow-up is completed. Additionally, follow-up assessments will be performed at 2 years  $\pm$  30 days, 3 years  $\pm$  30 days, 4 years  $\pm$  30 days, and 5 years  $\pm$  30 days postoperatively to evaluate the long-term safety of the investigational product.

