### **7.1.7 Safety Evaluation Methods**

#### **7.1.7.1 Description of Safety Parameters**

Safety endpoints:

**7.1.7.1.1** At discharge or 30 days postoperatively (whichever comes first), 3 months, 6 months, and 12 months:

- Incidence of serious adverse events, including cardiovascular death, major

bleeding, severe damage to cardiac or other body structures, infective endocarditis, and thromboembolic events related to the trial device.

- All-cause mortality.
- Cardiovascular death related to the trial device.
- Major bleeding related to the trial device.
- Severe damage to cardiac or other body structures related to the trial device.
- Infective endocarditis related to the trial device.
- Thromboembolic events related to the trial device.

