## **7.2.7 Clinical Evaluation at 2, 3, 4, and 5 Years ( $\pm 30$ Days) Postoperatively**

**7.2.7.1** Telephone follow-up.

**7.2.7.2** Record adverse events.

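### Named device harms and mortality are compared between arms only to 12 months; the one 5-year comparison, any adverse event, is insensitive to late device harm

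*Protocol*

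**What the plan says.** Protocol section 3.2 sets follow-up at 2, 3, 4 and 5 years "to evaluate the long-term safety of the investigational product". Section 7.1.7.2.2 has safety evaluated "annually from 2 to 5 years postoperatively, recording all adverse events", and section 7.2.7 makes these contacts by telephone.

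The safety endpoints are tied to earlier times. Section 7.1.7.1.1 places device-related serious adverse events, all-cause mortality, device-related cardiovascular death, major bleeding, structural damage, endocarditis and thromboembolism under "At discharge or 30 days postoperatively (whichever comes first), 3 months, 6 months, and 12 months". Section 7.1.8.4 does the same. The comparisons in sections 8.1.6.2.1 to 8.1.6.2.7 follow that schedule, for example "The incidence of all-cause mortality at discharge or 30 days, 3 months, 6 months, and 12 months post-surgery will be compared" and "The incidence of device-related infective endocarditis at discharge or 30 days, 3 months, 6 months, and 12 months post-surgery will be compared".

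One between-arm comparison goes further, section 8.1.6.2.8: "The incidence of adverse events from postoperative to 5-year follow-up will be compared", by chi-square or Fisher's exact test. Section 8.1.6.3 also summarises device-related and serious treatment-emergent events by severity, system organ class and preferred term, with no end date.

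**The concern.** For a permanent implant, the later years are where endocarditis, thrombosis, recurrent regurgitation and reoperation (complications of the kind listed in section 6.5) could separate the two rings. Four of the five follow-up years lie beyond the last time point of every named safety endpoint. Not even death is compared after month 12.

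The comparison that does reach 5 years uses a poor measure. Section 13.1 defines an adverse event broadly: it need not be related to the device, and mild events count. Counting starts at the operation. A patient who had any minor event in the first weeks is already a case, so endocarditis or death in year 3 leaves that patient's result unchanged. At stake is the stated purpose of years 2 to 5. The primary endpoint is not affected.

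**Working it through.** **Inputs from the protocol.** 82 patients per arm (section 8.2.1); about 10% dropout (section 8.4), so 82 × 0.90 = 73.8, about 74 per arm; two-sided tests at 0.05 (section 8.3); chi-square or Fisher's exact test (section 8.1.6.2.8). The protocol states no figure for the safety comparisons, so there is none to reproduce. The arm size rests on the primary endpoint, and its 75 per group does reproduce (95% success in both arms, margin 10 points, one-sided 0.025, power 80%).

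**Assumed inputs, because the protocol gives none.** b is the chance of at least one unrelated adverse event by 5 years, taken as 50% to 90%. h is the 5-year rate of a late device harm, taken as 5% in control against 15% or 20% in test, with 2% against 5% as a low-rate case. The two are taken as independent.

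**Step 1, dilution.** The proportion with any adverse event is 1 − (1 − b)(1 − h). The between-arm difference therefore shrinks from (h_test − h_control) to (1 − b)(h_test − h_control). With b = 80% and harm of 15% against 5%:

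- control: 1 − 0.20 × 0.95 = 0.81
- test: 1 − 0.20 × 0.85 = 0.83

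A 10-point difference in harm becomes a 2-point difference in any adverse event.

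**Step 2, power.** Exact power of Fisher's two-sided test, 82 per arm:

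| Late harm, test vs control | Harm compared directly | Any AE, b = 50% | b = 70% | b = 80% | b = 90% |
|---|---|---|---|---|---|
| 15% vs 5% | 0.495 | 0.072 | 0.050 | 0.039 | 0.031 |
| 20% vs 5% | 0.805 | 0.124 | 0.072 | 0.052 | 0.036 |
| 5% vs 2% | 0.063 | 0.038 | 0.035 | 0.031 | 0.029 |

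With 74 per arm, direct power for the first two rows falls to 0.437 and 0.752; any-AE power at b = 80% is 0.037 and 0.048.

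**Reading.** Where late harm differs substantially, the any-event comparison is close to uninformative even if only half the patients have a background event. Where late harm is rare in both arms, neither comparison has useful power.

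**The case against.** The strongest reply is that nothing is lost. All adverse events are recorded each year to 5 years, the event committee's judgement of device-relatedness (section 7.1.7.2.1) has no end date, and section 8.1.6.3 tabulates device-related and serious events without a 12-month limit. This stands against two readings that are tempting. A reader might infer that the data collected cannot answer the long-term question; they largely can, because the gap lies in the endpoints and comparisons specified. A reader might also infer that device harms stop being analysed at 12 months; they do not, but afterwards they appear only as descriptive summaries by organ class and preferred term. Those are not the defined endpoints: major bleeding by its BARC grade and cardiovascular death by its VARC definition cannot be read off preferred terms.

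Other points also have force.

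- No rate supports saying that nearly every patient will have an adverse event. The argument does not need it, since it already holds at 50%.
- Nothing in the protocol says the rings would be declared alike after a non-significant safety test.
- For tricuspid reoperation, section 7.1.8.1 stops at 12 months, but the analysis in section 8.1.6.1.4 names no time. That is an ambiguity, not a clear cut-off.
- The registration report follows the 6-month visit, so it is not affected.

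The reply that this belongs in the statistical analysis plan is weaker. That plan is not shown and may add tables, but the protocol itself fixes the endpoint times and itself chooses the one 5-year comparison.

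**Conclusion.** The point holds as a cheap improvement. Between-arm comparison of the named device harms and of all-cause mortality ends at 12 months, and the only one running to 5 years is a measure that early, unrelated events can fill. Under assumed late harm of 15% against 5%, that measure has about 7% to 3% power over a 50% to 90% background, against about 50% for the harm itself; for 20% against 5%, about 12% to 4% against about 81%. These figures rest on assumed rates, independence of background events and device harm, and 82 per arm with complete follow-up. They show the insensitivity of the measure; they do not forecast this trial. At 5% against 2% the direct comparison has only about 6% power, so the case for change is that the right events are reported with intervals.

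**What to change.** - In sections 7.1.7.1.1, 7.1.8.4 and 8.1.6.2.1 to 8.1.6.2.7, add the 2-, 3-, 4- and 5-year time points for the named safety endpoints and all-cause mortality.
- State in sections 7.1.8.1 and 8.1.6.1.4 that freedom from tricuspid reoperation is also reported to 5 years.
- In section 8.1.6.2.8, report these events by arm with the difference and its 95% CI, and keep any adverse event as a descriptive count.

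This needs no new visits or tests. It uses the event reports that the yearly telephone contacts already collect and the existing event committee. The cost is protocol wording, a few more tables and some adjudication of late events. One limit remains: the schedule in section 7.2.8 has no echocardiography in years 2 to 5, so silent degeneration of the repair will not be detected, and the report should say so.
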